## Abstract

**Introduction:**

Radiofrequency ablation is a cornerstone therapy for patients with ischemic cardiomyopathy (ICM) presenting with ventricular tachycardia (VT). In this context, ablation is typically performed endocardially as a first‐line approach. However, despite acute procedural success, the risk of recurrence remains high, potentially due to the presence of epicardial substrate. Several observational studies have suggested the potential benefits of a first‐line endo‐epicardial approach in decreasing recurrence. In this context, the EPIC‐VT trial was designed to compare endocardial‐only ablation versus combined endo‐epicardial ablation as a first‐line approach in ICM patients with VT.

**Methods:**

The EPIC‐VT trial is a prospective, multicenter, controlled, randomized, open‐label superiority trial with two parallel groups (endocardial‐only approach vs*.* combined endo‐epicardial approach) in a 1:1 ratio. The primary objective of this study is to demonstrate that a combined endo‐epicardial approach reduces the risk of VT recurrence compared to an endocardial approach alone in patients with ICM. Patients will be followed for 2 years after the procedure.

**Results and Conclusion:**

To date, only retrospective studies have compared VA recurrences in patients with ICM, depending on whether ablation was performed using an endocardial or an endo‐epicardial approach, with conflicting results. A meta‐analysis suggested an advantage of the endo‐epicardial approach over the endocardial approach (odds ratio = 0.39 [95% CI: 0.18–0.83]). However, the level of evidence remains low, and no controlled randomized study has confirmed this hypothesis. If the EPIC‐VT study confirms the superiority of a first‐line endo‐epicardial approach, such strategy could become the preferred option for VT ablation in ICM, thereby reducing the risk of VA recurrence.

AbbreviationsATPantitachycardia pacingCABGcoronary artery bypass graftingCRFcase report forme‐CRFelectronic case report formICDimplantable cardiac defibrillatorLVleft ventricleMRImagnetic resonance imagingPFApulsed field ablationVFventricular fibrillationVTventricular tachycardia

## Introduction

1

Patients with ischemic cardiomyopathy (ICM) are at significant risk of ventricular tachycardia (VT), which causes substantial morbidity and mortality [1]. Primary prevention of arrhythmia‐related mortality largely involves implantation of an automatic implantable cardioverter‐defibrillator (ICD) [2]. However, while ICDs effectively terminate arrhythmias, they do not prevent them, and device therapies are associated with considerable morbidity and mortality. Medical therapy using antiarrhythmic drugs (AAD) is a common antiarrhythmic strategy in this population; however, their efficacy remains limited. In cases where AAD are ineffective or poorly tolerated, radiofrequency ablation has emerged as an efficient alternative to reduce arrhythmia recurrences [3]. In the context of ICM, ablation is typically performed using a first‐line endocardial approach, accessing the left ventricle (LV) either retrogradely or transeptally [4]. However, despite achieving acute success during the procedure, the VT recurrence rate remains non‐negligible during follow‐up, with 40%–50% of patients experiencing at least one recurrence within the 2 years after the procedure [5, 6, 7, 8]. These recurrences may be due to an inability to create transmural lesions. In fact, with an endocardial approach, ablation lesions are created only within the LV, whereas a significant portion of the arrhythmogenic substrate may be located on the other side of the myocardial wall, on its epicardial surface [9].

First described in 1996, epicardial ablation has since seen significant developments [10]. The clinical efficacy of epicardial ablation, along with technological advancements and increased operator experience, has allowed this technique to become more widely used, and is now regularly performed in certain clinical situations [11, 12, 13]. Indeed, a dual endo‐epicardial approach is commonly used as first‐line treatment for VT associated with primary dilated cardiomyopathy, myocarditis, or arrhythmogenic right ventricular dysplasia, where the arrhythmogenic substrate is frequently epicardial [11, 12, 13]. A benefit in reducing the risk of recurrence has been demonstrated, with a low complications rate in experienced centers [11].

In contrast, for VT associated with ICM, the combined endo‐epicardial approach is usually reserved for patients with recurrent VT despite one or more endocardial procedures and is not currently considered a first‐line treatment. However, epicardial involvement is often present in ICM VTs [9]. Several retrospective studies [14, 15, 16, 17, 18, 19] and meta‐analyses [20, 21] suggested a significant benefit of the endo‐epicardial approach compared with the endocardial‐only approach. However, the level of evidence remains low, as no randomized trials have confirmed these results.

The aim of our prospective, multicenter, randomized controlled trial is to compare the time to VT recurrence following first‐line ablation in ICM using either an endocardial‐only or a combined endo‐epicardial approach. The findings of this study could establish a new treatment paradigm for managing VA in ICM patients.

## Methods

2

### Study Design

2.1

The EPIC‐VT trial is a prospective, multicenter controlled, randomized, open‐label superiority study with two parallel groups, randomized in a 1:1 ratio. The trial includes 13 centers across France (Angers, Bordeaux, Brest, Caen, Clermont‐Ferrand, Lille, Lyon, Nantes, Paris La Pitié Salpêtrière, Paris Hôpital Européen Georges Pompidou, Rennes, Tours). Patients with ICM requiring a first radiofrequency ablation for VT will be randomized to endocardial‐only ablation or combined endo‐epicardial ablation. The study was approved by the Ethics Committees and complies with the principles of the Declaration of Helsinki. Patient recruitment began on October 23, 2023 (first patient recruitment), and is expected to be concluded on October 23, 2028. The duration of study participation for each patient will be up to 24 months from the date of the ablation procedure, while the total study duration will span 60 months.

### Patient Population

2.2

Participation in the study may be offered to ICM patients requiring VT radiofrequency ablation, either during consultation (outpatient) or during hospitalization (for inpatients requiring urgent intervention). Participation in the study will be proposed and explained to the patient along with the provision of an information letter. Signed informed consent will be obtained before patients are randomized. Antithrombotic treatment will be adapted according to the randomization group. Randomization will be centralized through the Ennov software (Ennov Clinical, Groupe Ennov, Paris, France), generating blocks of variable size to ensure the unpredictability of treatment allocation. The block sizes and order of treatment within each block will be randomly generated. Randomization will be stratified by center.

Patients must meet the following criteria to be eligible for the study: (i) patients aged > 18 years, (ii) requiring first‐time radiofrequency ablation for VT associated with ICM, (iii) implanted with an ICD and monitored remotely through telemonitoring, (iv) for women of childbearing age, use of effective contraception until hospital discharge, (v) provision of written informed consent, and (vi) affiliated with a health insurance system or benefiting from such coverage.

Patients meeting any of the following criteria will be excluded from the study: (i) history of cardiac surgery compromising epicardial access (such as coronary artery bypass grafting, valve replacement, or other surgeries that may have caused pericardial adhesions), (ii) presence of a left ventricular thrombus detected on pre‐procedure imaging, (iii) use of anticoagulant therapy that cannot be temporarily discontinued, (iv) use of dual antiplatelet therapy that cannot be temporarily replaced by single antiplatelet therapy, (v) history of pericarditis, (vi) history of thoracic radiotherapy, (vii) contraindication to general anesthesia, (viii) pregnant or breastfeeding women, (ix) history of type 2 heparin‐induced thrombocytopenia (as heparin injection is required during the procedure), and (x) adults under legal protection (e.g., guardianship, curatorship), deprivation of liberty, or inability to provide informed consent.

### Intervention

2.3

The aim of this study is to assess whether combined endo‐epicardial radiofrequency ablation is superior to the conventional endocardial approach as a first‐line treatment for ICM patients requiring VT ablation.

#### Preoperative Assessment

2.3.1

Imaging (such as a cardiac computed tomography (CT) scan with contrast injection, contrast echocardiography, or transesophageal echocardiography) will be performed within the month before the procedure to rule out the presence of an intraventricular thrombus, which would contraindicate endocardial access. If an intraventricular thrombus is detected in a patient not receiving anticoagulant therapy, the procedure will be postponed until the thrombus resolves. A second preoperative imaging will be performed to confirm clearance of the thrombus before proceeding.

Cardiac magnetic resonance imaging (MRI) will not be systematically performed as part of the screening process, as its spatial resolution may be insufficient to definitively exclude epicardial or midmyocardial substrate, and many patients with ICDs may have suboptimal MRI quality or contraindications to MRI. However, in cases where MRI was performed before the procedure, a secondary analysis will be conducted to evaluate its predictive value in identifying epicardial or midmyocardial substrate.

Before the procedure, a clinical examination and standard preoperative blood test will be performed. The procedure will be performed under local anesthesia with light sedation, if needed, or under general anesthesia, depending on the patient's preference and logistical considerations at each center.

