#### Data Collection

2.5.1

The measurement time points for each assessed parameter are shown in Table 1. Descriptive data for the study population will be collected before the ablation procedure. These data will be presented using descriptive statistics.

**Table 1 jce16630-tbl-0001:** EPIC‐VT protocol.

	Inclusion visit		Randomization	D‐1		Radiofrequency Ablation	Before hospital discharge		6‐month follow‐up phone call^a^ (M6 ± 1 month)		12‐Month consultation (M12 ± 1 month)		18‐month follow‐up phone call^a^ (M18 ± 1 month)		24‐Month consultation (M24 ± 1 month)		Data collection post 24 months	
Actions	CP	AR		CP	AR		CP	AR	CP	AR	CP	AR	CP	AR	CP	AR	CP	AR
Information and Consent		X																
Verification of Selection Criteria		X																
Pregnancy Test		X																
Verification of Medical History	X																	
Standard Preoperative Biological Assessment				X														
Echocardiography							X											
Clinical Examination	X			X			X											
ICD Interrogation							X											
Medications Taken	X			X			X			X		X		X		X		
Imaging (Exclusion of Thrombus)				X^b^														
Inquiry About Adverse Events							X			X								
Remote monitoring (VT/VF episodes)										X		X		X		X		X

Abbreviations: CP = clinical practices, AD = added by the Research.

^a^
or during a scheduled consultation;

^b^
From 1 Month to 1 Day Before.

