#### Statistical Analysis

2.7.2

Statistical analyses will be performed using the biometry unit of the Center of Clinical Investigation of Rennes. Interim analyses will not be performed. Patients randomized and undergoing ablation will be analyzed on a “modified intention‐to‐treat” basis. Only patients with a persistent left intraventricular thrombus that definitely contraindicates ablation will be excluded. The expected exclusion rate is very low ( < 3%) and exclusion is not expected to be dependent on the allocated treatment arm. The clinicopathological criteria at inclusion will be described for all patients as well as for each of the two study arms: (i) qualitative variables will be presented as counts and percentages, and (ii) quantitative variables will be presented as means, standard deviations, quartiles, minimums, and maximums. The normality of the distribution of quantitative variables will also be assessed graphically and/or using the Shapiro‐Wilk test, if necessary. The primary endpoint is a censored variable; therefore, both groups will be compared using the log‐rank test. Secondary endpoints will be analyzed according to the type of variable: (i) quantitative variables will be analyzed using the Student's *t*‐test or the Mann–Whitney test if necessary; (ii) qualitative variables will be analyzed using the Chi‐square test or Fisher's exact test if necessary; (iii) censored variables will be analyzed using the Log‐rank test.

Adjustments may be made in cases with heterogeneity at inclusion. The conditions for applying these tests or models will be verified before their implementation. All the tests will be conducted at a significance level of 5%.

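### Minor: the scan that decides the thrombus exclusion may follow randomization, and the thrombus criterion conflicts with the postpone-and-rescan rule for a thrombus that clears

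*Protocol article*

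**What the plan says.** **Eligibility.** Section 2.2 lists among the exclusions "ii) presence of a left ventricular thrombus detected on" pre-procedure imaging, with no condition about persistence. Patients may be outpatients or come from hospital, the latter described as "for inpatients requiring urgent intervention". Consent must precede randomization. No such rule is stated for the scan.

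**Schedule.** In Table 1 (section 2.5.1) the row "Verification of Selection Criteria" is marked at the inclusion visit, before the randomization column. The row "Imaging (Exclusion of Thrombus" is marked as routine care under D-1, after it. Footnote b gives the window: "From 1 Month to 1 Day Before".

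**Handling a finding.** Section 2.3.1 ties the scan to the month before the procedure and states: "If an intraventricular thrombus is detected in a patient not receiving anticoagulant therapy, the procedure will be postponed until the thrombus resolves". A second scan must then confirm clearance.

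**Analysis.** Section 2.7.2 defines a modified intention-to-treat set: "Only patients with a persistent left intraventricular thrombus that definitely contraindicates ablation will be excluded". It expects this in fewer than 3% of patients and adds that "exclusion is not expected to be dependent on the allocated treatment arm".

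**The concern.** There are two linked problems.

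1. **Order.** A patient whose persistent thrombus is found after allocation leaves the analysis as a post-randomization exclusion. Had the same patient been scanned before allocation, he or she would not have been randomized. The trial is open-label, so whether a thrombus definitely rules out ablation can be judged with the arm known. The plan relies on an expectation that such exclusions do not depend on arm, where scanning first would secure this by design for the patients concerned.
2. **Wording.** Read literally, criterion (ii) excludes a patient whom sections 2.3.1 and 2.7.2 would treat and analyse. A multicentre trial needs one rule.

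At stake are the cleanness of the randomized set and uniform handling across sites, not the main conclusion of the trial.

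**Working it through.** **Step 1: order of events.** Selection criteria are checked before randomization. The thrombus row sits after it, with a window counted back from the procedure. A scan early in that window could precede randomization and a late one could follow it. Both orders are permitted. Section 2.7.2 plans for exclusions of this kind from the analysis set.

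**Step 2: the three rules side by side.**

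| Patient with a thrombus on the scan | Section 2.2, criterion (ii) | Section 2.3.1 | Section 2.7.2 |
|---|---|---|---|
| Not anticoagulated, clears | Excluded | Postponed, rescanned, ablated | Analysed |
| Not anticoagulated, persists | Excluded | Stays postponed | Excluded if ablation is definitely contraindicated |
| Already anticoagulated | Excluded | No rule given | Excluded if persistent and ablation is definitely contraindicated |

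The open conflict is in the first row. The word persistent occurs only in section 2.7.2. Section 2.3.1 carries the same idea by waiting for resolution, and only for patients not on an anticoagulant.

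**Step 3: how many patients.** 0.03 × 150 = 4.5, and the rate is stated as below 3%, so at most 4 patients. 4/150 = 2.7%, about 2 per arm if evenly split. The document gives no rate for thrombi that clear, so none is estimated here.

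**Step 4: power.** Inputs from section 2.7.1: HR 0.43, two-sided 5%, 90% power, 59 events, 150 patients, 2-year recurrence 50% and 26%. Allocation is 1:1 (section 2.1).

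The plan's own figure first, by Schoenfeld: D = 4(1.960 + 1.282)²/(ln 0.43)² = 4 × 10.507/0.7123 = 59.0. At 59 events the power is 90.0%, so the stated figure is reproduced.

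Power at D events = Φ(√D × 0.844/2 − 1.960).

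- Two-year events only, n = 150: 75 × (0.50 + 0.26) = 57.0 events, power 89.0%.
- Two-year events only, n = 146: 73 × 0.76 = 55.5 events, power 88.2%.

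Section 2.7.1 also continues remote ICD follow-up to the last patient's last visit. Assume exponential hazards λ = −ln(0.50)/24 and −ln(0.74)/24 per month, and uniform accrual over A months. The event probability in an arm is then 1 − (e^(−24λ) − e^(−(24+A)λ))/(Aλ).

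| Assumption | n = 150 | n = 146 |
|---|---|---|
| A = 36 (60-month study less 24), no loss | 82.0 events, 96.9% | 79.8 events, 96.5% |
| A = 60 (recruitment October 2023 to October 2028), no loss | 93.2 events, 98.3% | 90.7 events, 98.0% |
| A = 36, assumed 10% a year death or loss | 70.4 events, 94.3% | 68.5 events, 93.7% |

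As an example, for A = 36 the event probabilities are 0.6891 and 0.4046. Then 75 × 1.0937 = 82.0 and 73 × 1.0937 = 79.8.

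Removing 4 patients costs 0.3 to 0.8 percentage points throughout. With the extended follow-up, expected events stay above 59 in every scenario shown.

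**The case against.** The other side has a good deal to say.

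- **The exclusion is disclosed, narrow and bounded.** Section 2.7.2 names it, limits it to thrombi that definitely rule out ablation, and expects it not to depend on arm. Both arms need left ventricular endocardial access. This stands, and it is why the point is minor.
- **A scan close to the procedure has a purpose.** It protects endocardial access, and an early scan can go stale while antithrombotic treatment is adjusted after allocation. This also stands. The fix therefore keeps the one-month window and accepts an occasional repeat scan.
- **The wording can be reconciled.** The second, clear scan is also pre-procedure imaging, so criterion (ii) could be applied to that one. This is a workable reading, but the criterion turns on detection and does not say so.
- **The article is a condensed version.** The full protocol may schedule the scan differently. That is possible, but the table shown does place eligibility checking and the scan on opposite sides of randomization, so this is a stated order and not just missing detail.
- **The fix leaves some cases open.** True for urgent inpatients and slipped procedures. It reduces these exclusions without abolishing them.

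A reader might infer bias, because antithrombotic drugs are interrupted for longer in the combined arm (sections 2.3.2 and 2.3.3) and the scan may come one day before the procedure. That is a reason to close the gap. The document contains nothing showing that thrombus findings or removals differ by arm. A reader might also infer that most of the exclusions are avoidable. The document gives no interval from randomization to procedure, no share of scans done late and no share of urgent inpatients, so only some can be claimed.

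**Conclusion.** The point holds as a minor, inexpensive improvement. The schedule allows an exclusion criterion to be decided after open-label allocation, and criterion (ii) contradicts sections 2.3.1 and 2.7.2 for one group: patients not on an anticoagulant whose thrombus clears. At most 4 of 150 patients are affected as exclusions, taking the protocol's own bound and 150 as the number randomized. Some of those could be avoided. The power cost is under 1 percentage point under every assumption tried, so no material loss is shown, and the primary comparison is not called into question.

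**What to change.** 1. **Table 1.** Require the thrombus scan before randomization whenever feasible, still within one month of the procedure, and randomize only once no thrombus is present.
2. **When the scan has to follow randomization** (urgent inpatients, or a repeat because the procedure slipped), apply sections 2.3.1 and 2.7.2 as they stand.
3. **Criterion (ii).** Reword along these lines: *left ventricular thrombus on pre-procedure imaging, unless the patient was not on an anticoagulant and the second scan (section 2.3.1) shows that the thrombus has cleared*. This leaves exclusion on detection unchanged for patients already anticoagulated. A plain condition of persistence on repeat imaging would end it for them, although section 2.3.1 gives them no rescan step.

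**Cost.** One table entry and one exception clause, made as an amendment while enrolment is under way (section 2.8), plus tighter scheduling and an occasional repeat scan. The endpoint, the analysis-set rule and the sample size do not change, and patients already randomized remain covered by sections 2.3.1 and 2.7.2.

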#### Endocardial Approach Only

2.3.2

Regarding antithrombotic management: (i) for patients on direct oral anticoagulants (DOACs), the morning dose (apixaban, dabigatran, or morning dose of rivaroxaban) or the evening dose (evening dose of rivaroxaban) will be withheld; (ii) for patients on vitamin K antagonists (VKAs), the procedure will be performed if the international normalized ratio (INR) is < 3 on the day before the procedure; and (iii) for patients on antiplatelet agents, the procedure will be performed regardless of the combination of antiplatelet therapy.

The defibrillator will be deactivated at the beginning of the procedure. Endocardial access to the left ventricle will be obtained via a retrograde aortic approach (through femoral arterial puncture) and/or a transseptal approach (through femoral venous puncture) according to the center's usual practice and the presumed location of the VT. A quadripolar catheter will be placed inside the right ventricle to pace the ventricle during the procedure if needed for VT induction/overdrive and to perform programmed ventricular stimulation at the end of the procedure.

Unfractionated heparin will be administered at the beginning of the procedure (100–120 IU/kg) and then regularly during the procedure to maintain an activated clotting time (ACT) of approximately 300 s.

The procedure will be performed using conventional 3D mapping techniques. A high‐density map during sinus rhythm or pacing will be created at the beginning of the procedure to identify low‐voltage areas and the presence of late potentials, abnormal ventricular electrograms, and deceleration zones. VT induction will be attempted if desired to perform an activation map. A complete substrate ablation strategy will be employed, supplemented by specific strategies for the ablation of induced VTs (pace mapping and entrainment mapping). Radiofrequency energy will be delivered using irrigated tip catheters at 30–50 W, preferably with isotonic saline, for a maximum duration of 60 s.

At the end of the procedure, programmed ventricular stimulation will be used to assess the inducibility of clinical or other nonclinical VTs, thereby determining the acute success or failure of the procedure. A standardized protocol will be followed, with stimulation at two different cycle lengths (600 and 400 ms) and up to three extrastimuli decrementing to 200 ms (or the ventricular refractory period). For non‐inducible patients, the procedure will be concluded. For patients with inducible VTs, ablation will continue, specifically targeting the induced VTs.

Acute procedural success will be defined by both the absence of VT inducibility on programmed ventricular stimulation and complete substrate modification, including the elimination of arrhythmogenic sites such as local abnormal ventricular activities. To confirm the efficacy of substrate modification, systematic postablation remapping will be performed.

Crossover to an epicardial approach will not permitted during the index procedure. If VT remains inducible despite endocardial ablation, patients will continue follow‐up as per protocol. Any recurrence of VT will be considered as meeting the primary outcome, and subsequent management, including potential epicardial access, will be left to the discretion of the treating physician outside of the initial study intervention. Patients will be analyzed on an intention‐to‐treat basis.

The defibrillator will be reactivated at the end of the procedure.

